## Abstract

**Background:**

The success rate of infertility treatments remains modest. Endometrial injury has been suggested as an intervention to increase the probability of pregnancy in women undergoing assisted reproductive technologies such as in vitro fertilisation (IVF). The majority of studies and systematic reviews have reported that endometrial injury improves the outcome**s** of IVF, intrauterine insemination and natural conception; however, the size and quality of the studies are poor. The low quality of the available evidence questions the presence of any real beneficial effect, and the applicability of the intervention in different populations remains unclear.

**Methods/design:**

The PIP trials are three multi-centre, randomised controlled trials designed to test three separate hypotheses: whether endometrial injury increases the probability of live birth in women or couples

1) who are undergoing autologous embryo transfer as part of an IVF cycle (PIP-IVF),

2) with unexplained infertility who are attempting to conceive naturally (PIP-UE) and

3) with subfertility related to polycystic ovarian syndrome (PCOS) who are on ovulation induction medication and attempting to conceive (PIP-PCOS).

Participants will be randomised to either undergo endometrial injury by endometrial pipelle biopsy or to:

• no intervention (PIP-IVF), or

• a sham procedure (PIP-PCOS and PIP-UE).

In PIP-IVF, endometrial injury will be carried out between day three of the cycle prior to the IVF cycle, and day three of the IVF cycle. In PIP-UE and PIP-PCOS, endometrial injury or a sham procedure will be undertaken between days 1–12 of a menstrual cycle or ovulation induction cycle respectively. Participants in PIP-UE and PIP-PCOS will then be followed for three cycles during which time they will attempt to conceive from sexual intercourse. To ensure allocation concealment, randomisation will be carried out using a web-based system or sequentially numbered, opaque, sealed envelopes. The primary outcome is live birth. Secondary outcomes include ongoing pregnancy, clinical pregnancy and miscarriage.

The required sample sizes for the PIP studies have been estimated at 840 (PIP-IVF), 350 (PIP-UE) and 280 (PIP-PCOS). Primary analysis will be as per intention-to-treat principles.

**Discussion:**

The PIP trials are designed to address the gaps in the utility of endometrial scratching as a treatment for subfertility in three different populations. If the beneficial effect of this intervention can be confirmed in these settings, endometrial scratching will provide a cost-effective method for helping women and couples to conceive.

**Trial registrations:**

PIP-IVF ACTRN12614000626662 registered 13/6/2014; PIP-PCOS ACTRN12614000657628 registered 24/6/2014; PIP-UE ACTRN12614000656639 registered 24/6/2014. The trials are ongoing.

## Background

Having a baby is an important goal for many couples. Unfortunately, up to 10 % of couples will not achieve pregnancy after a year of frequent, unprotected intercourse and are defined as being subfertile [1]. Many subfertile couples seek fertility treatments to help them conceive. However, even the most successful fertility treatment, in vitro fertilisation (IVF), has a live birth rate of only 30 % per cycle [2, 3]. Failure of an IVF cycle to result in pregnancy can be due to a number of factors and, even when high quality embryos are replaced, implantation rates remain modest. A lack of adequate endometrial receptivity is thought to be responsible for up to two-thirds of unsuccessful embryo transfers [4].

Endometrial injury is currently being proposed as a technique to improve the endometrial receptivity and in turn the probability of conception in IVF cycles. Endometrial biopsy is the most common procedure used to deliver an endometrial injury [5]. The procedure involves the insertion of a catheter, such as a pipelle sampler, through the cervix and into the uterus, where a sample of the endometrium is obtained via light suction and rotation within the uterine cavity. The biopsy results in a ‘scratch’ or ‘injury’ to the endometrium during the process of obtaining a sample. Outside of the fertility area, pipelle biopsy is routinely performed to collect endometrial samples for diagnostic purposes, for example, in women with abnormal menstrual bleeding. It is a well-tolerated procedure with a proven safety profile [6, 7].

In 2000 it was first reported in a retrospective study that 11 of 12 women who had undergone a series of investigational endometrial biopsies conceived in their subsequent IVF cycle [8]. A prospective non-randomised study by the same research group reported that women allocated to endometrial biopsy in the cycle prior to IVF cycle were twice as likely to conceive as women who had not [9]. Several studies have since investigated the apparent beneficial effect of endometrial injury in IVF cycles, and although there is substantial heterogeneity in the study designs and participant populations, a recent Cochrane review including randomised controlled trials (RCTs) reports an increase in the probability of pregnancy and live birth following endometrial sampling in the cycle preceding embryo transfer (RR = 1.34, 95 % CI 1.21–1.61 and RR = 1.42, 95 % CI 1.08–1.85, respectively) [5]. Other reviews and meta-analyses which have included both RCTs and non-randomised studies have similar conclusions [10–12]. The effect appears to be the most pronounced in women who have repeatedly failed to achieve a pregnancy after multiple embryo transfers, that is, women with recurrent implantation failure (RIF) [13]. Note that in the only study where endometrial injury was performed on the day of oocyte retrieval, a detrimental effect on pregnancy rate was observed [14].

Almost all of the RCTs assessing endometrial injury are associated with significant limitations that place them at a high risk of bias, which is known to be associated with exaggerated effect estimates (such as lack of adequate blinding and allocation concealment, high rates of participant attrition), or raise questions regarding the generalisability of results (such as use of multiple embryo transfer policies or ovulation induction medications in couples with unexplained infertility, timing of endometrial injury, and the device used for causing endometrial injury). Another common issue in a number of the studies is the potential exposure of the control group to unintentional endometrial injury resulting from a placebo procedure [15–17] or a co-intervention such as hysteroscopy, either prior to study enrolment [18] or simultaneously with the study procedure [19, 20]. Finally, only a small proportion of the studies reported live birth, arguably the most important outcome for both clinicians and subfertile couples.

The mechanism by which endometrial injury may increase the probability of conception has been the topic of a number of studies and speculations, and is extensively summarised in recent reviews [10, 21]. The most frequently cited theory is that of inflammation. Endometrial scratching has been shown to induce an inflammatory response in the endometrium, which is believed to mediate the dialogue between the endometrium and the blastocyst and facilitate the process of implantation [22]. The resultant inflammatory response involves the production of inflammatory cytokines and subsequent recruitment of macrophages and other immune cells, factors known to be present during the window of implantation. This hypothesis is supported by repeat biopsy studies, in which women who had undergone a second biopsy had increased levels of cytokines such as TNF-α and MIP-1B, and other molecules known to be associated with implantation, such as osteopontin [22–25]. It is possible that endometrial injury may also be beneficial in women with unexplained infertility or polycystic ovarian syndrome (PCOS) who are trying to conceive from sexual intercourse; conditions of infertility in which poor endometrial receptivity has been implicated [26–30].

Due to the generally poor quality of the published studies and a lack of a clear understanding regarding the underlying mechanism of effect, the reproductive benefit of endometrial injury remains controversial [5, 31–34]. This protocol describes studies to be undertaken in three separate groups of women in whom inadequate endometrial receptivity may be partly responsible for the experienced infertility: unexplained infertility, PCOS and women undergoing embryo transfer as part of an IVF/intracytoplasmic sperm injection (ICSI) cycle.

Endometrial biopsy is a simple, cheap and well-tolerated procedure which can be performed without anaesthetic in the out-patient setting [6, 7]. Endometrial biopsy may be a cost-effective method for increasing the probability of pregnancy and live birth in women or couples who are undergoing IVF or who are trying to conceive naturally or with ovulation induction.

### Research questions

The Pipelle for Pregnancy (PIP) studies will evaluate whether endometrial injury delivered by an endometrial pipelle biopsy procedure increases the probability of live birth inWomen undergoing autologous embryo transfer; a fresh transfer as part of an IVF cycle or a frozen-thaw embryo transfer (PIP-IVF)Couples with unexplained infertility attempting to conceive spontaneously (PIP-UE)Couples with subfertility associated with polycystic ovarian syndrome who are on ovulation induction medication and trying to conceive (PIP-PCOS).

## Methods/design

The PIP studies are pragmatic, parallel, multi-centre, superiority RCTs.

The pragmatic nature of the studies is a result of the broad inclusion criteria, time frame in which the intervention is administered and lack of restriction to specific stimulation or ovulation induction protocols. This rationale is based on the existing evidence in favour of endometrial scratching before IVF, in which a benefit has been shown across a range of time frames for performing the intervention and in different patient populations. Inclusion of a heterogeneous population in a large study provides an opportunity to detect treatment effects within different patient subgroups.

### Blinding

PIP-IVF is an open label study; women will be aware of their study allocation as they will be randomised to undergo either endometrial biopsy or no procedure.

PIP-PCOS and PIP-UE are single-blind studies; women will not be aware of their study allocations as they will be randomised to either an endometrial biopsy or a sham procedure (placement of the pipelle in the anterior fornix).

In all three studies, the doctor performing the procedure will necessarily be aware of the participant’s allocation.

### Outcomes

The primary outcome is live birth rate per woman randomised, as defined previously [35].

Secondary outcomes include:ongoing pregnancy per woman randomised (defined as continuing pregnancy diagnosed by ultrasonographic visualisation of one or more gestational sacs on or after 12 weeks gestation)clinical pregnancy per women randomised (defined as a pregnancy diagnosed by ultrasonographic visualisation of one or more gestational sacs, including ectopic pregnancy)biochemical pregnancy (defined as βhcg > 25 mIU/ml) PIP-IVF onlymultiple pregnancies per women randomised and per clinical pregnancy (defined as ultrasonographic visualisation of two or more gestational sacs or heartbeats)ectopic pregnancy per women randomised and per clinical pregnancy (defined as a pregnancy in which implantation takes place outside the uterine cavity)miscarriage per women randomised and per clinical pregnancy (defined as the spontaneous loss of a clinical pregnancy before 20 completed weeks of gestational age)neonatal characteristics (for example, gender, gestation at birth, malformations)placenta characteristics (placenta previa: major, placenta previa: minor, placental abruption, placenta accreta: previous uterine surgery, placenta accreta: no previous uterine surgery)pain during the procedure (as measured by a 10 cm visual analogue scale (VAS))bleeding the day following the procedure.

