##### PIP-UE

Current rates of pregnancy in women with unexplained infertility undergoing expectant management are approximately 3 % per cycle [44]. An expected increase in pregnancy rates to 9 % in the biopsy arm might be expected based on previous studies. With 3 months of expectant management, this equates to an expected cumulative difference of 25 % vs 9 % in the biopsy and sham arms respectively. With an adjustment for live birth rates, which are generally 19 % lower than pregnancy rates [45], the expected difference becomes 20 % vs. 7 %. At 90 % power and a significance level of 5 % in a two-sided test, 158 women are required in each arm (316 in total).

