### Statistical analysis

Demographic and baseline data will be compared between the two groups using the chi-squared test or *t*-test. Outcome data for the primary analyses will be treated in an intention-to-treat manner, such that all participants remain in the groups to which they were randomised. If no outcome data is available for the primary outcome of live birth, this will be imputed to assume that women with no outcome data did not have a live birth. Sensitivity analyses based on different assumptions may be used for secondary analyses. Per protocol analyses will be conducted as a secondary analysis.

For binary outcomes (for example, live birth), risk ratios will be calculated with associated 95 % confidence intervals and *p* values. ANOVA or logistic regression analysis will be used for the analysis of pre-specified subgroup effects. For continuous outcomes (such as pain), the mean difference will be calculated and the student’s *t*-test will be used.

Assessment of participant blinding will be performed using both James’ and Bang’s blinding indices [47, 48]. All statistical analysis will be performed using STATA or a similar statistical programme.

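### The general rule for binary outcomes, applied as written, puts p values on miscarriage, multiple and ectopic pregnancy per clinical pregnancy, which is not a randomised comparison if biopsy changes who conceives

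*Protocol article*

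**What the plan says.** The Outcomes section of the protocol article gives three secondary outcomes two denominators each. For miscarriage it reads "miscarriage per women randomised and per clinical pregnancy", and for ectopic pregnancy "ectopic pregnancy per women randomised and per clinical pregnancy". Multiple pregnancy is worded in the same way. Live birth, ongoing pregnancy and clinical pregnancy are counted per woman randomised only.

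The Statistical analysis section has a single rule for outcomes of this type: "For binary outcomes (for example, live birth), risk ratios will be calculated with associated 95 % confidence intervals and" p values. It does not exempt the per-clinical-pregnancy versions or call them descriptive. The intention-to-treat sentence in that section is limited in scope: "Outcome data for the primary analyses will be treated in an intention-to-treat manner".

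The PIP-UE sample size section states how far the trial expects the number of pregnancies to differ between arms. Per-cycle rates of 3% and 9% are carried over three cycles, and "this equates to an expected cumulative difference of 25 % vs 9 % in the biopsy and sham arms respectively".

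**The concern.** Randomisation balances the women allocated to each arm. It does not balance the women in each arm who become pregnant if the procedure influences who becomes pregnant. The women pregnant after biopsy would then be those who would have conceived anyway plus those who conceived because of the biopsy. The second group has no counterpart among the control-arm pregnancies.

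If the added pregnancies are more fragile, miscarriage per clinical pregnancy rises although no pregnancy was harmed. If they are sturdier, it falls, and a real harm could be masked. A p value on that ratio looks like randomised safety evidence and is not.

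This matters here because the section on interim analyses and safety monitoring names miscarriage and multiple gestations among the events to be actively recorded, and says that no data safety monitoring committee will be set up. The final between-arm comparison therefore carries much of the safety message.

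**Working it through.** **1. Inputs from the protocol article**
- PIP-UE sample size section: pregnancy "undergoing expectant management are approximately 3 % per cycle". For the biopsy arm: "An expected increase in pregnancy rates to 9 % in the biopsy arm might be expected based on previous studies".
- Same section: live birth is taken as 19% lower than pregnancy, in both arms. This is a pregnancy-to-live-birth shortfall, not a miscarriage rate. It serves below only as an illustrative baseline loss.
- Final PIP-UE size 350, allocated 1:1, so 175 per arm.

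**2. The plan's own figures, reproduced**
- Cumulative pregnancy over three cycles: 1 − 0.91³ = 24.6% and 1 − 0.97³ = 8.7%, stated as 25% and 9%.
- Live birth: 24.6% × 0.81 = 20.0% and 8.7% × 0.81 = 7.1%, stated as 20% and 7%.
- Two-proportion sample size for 20% against 7%, two-sided 5%, 90% power: 143.1 per arm (144 rounded up) without continuity correction and 158.1 (159 rounded up) with it. The stated 158 is reproduced with the correction.

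**3. Make-up of the per-pregnancy denominators (PIP-UE)**
- Pregnancies: 175 × 0.25 = 43.8 and 175 × 0.09 = 15.8. Unrounded rates give 43.1 and 15.3.
- Share of biopsy-arm pregnancies that are added: (25 − 9)/25 = 0.64. This assumes that every woman who would conceive after sham would also conceive after biopsy, and that the planned pregnancy rates refer to clinical pregnancies.

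**4. Selection alone**

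Let pregnancies that would occur anyway be lost at 19% in both arms, so biopsy neither harms nor protects any of them. Let the added pregnancies be lost at rate q. The documents do not give q, so it is varied.
- Per-pregnancy ratio = (0.36 × 0.19 + 0.64 × q)/0.19
- Per-woman ratio = (25/9) × per-pregnancy ratio

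| q (assumed) | Ratio per clinical pregnancy | Ratio per woman randomised |
|---|---|---|
| 5% | 0.53 | 1.47 |
| 10% | 0.70 | 1.94 |
| 19% | 1.00 | 2.78 |
| 30% | 1.37 | 3.81 |
| 40% | 1.71 | 4.74 |

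With the unrounded pregnancy rates the first and last per-pregnancy ratios are 0.52 and 1.71, and the per-woman ratio at equal loss is 2.82.

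**5. How often a nominal 5% test would reject**

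This uses a two-proportion normal approximation with a pooled standard error under the null. In PIP-UE (15.3 against 43.1 pregnancies) it gives about 18% at q = 5%, 10% at 10%, 5% at 19%, 7% at 30% and 15% at 40%. With so few pregnancies these are rough.

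PIP-IVF needs further assumptions: the same 19% baseline, and pregnancy rates from its planned live birth rates, 17%/0.81 = 21% and 33%/0.81 = 41%. With 420 per arm this is about 88 against 171 pregnancies. The ratio runs from 0.64 (q = 5%) to 1.54 (q = 40%), with rejection at about 32% and 42%; at q = 30% the ratio is 1.28 and rejection about 16%.

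No corresponding calculation was made for multiple or ectopic pregnancy. The argument is the same, but the documents give no baseline rate.

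**The case against.** The strongest reply has four parts.

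- **The test is inferred.** The Outcomes section lists denominators and names no test. The risk ratio and p value come from a general sentence whose example, live birth, is counted per woman. A separate analysis plan may settle which version is inferential. This stands as a limit on wording: the point is what follows if the general rule is applied as written. It does not remove the point, because that rule is the only one stated and it makes no exception.
- **The premise is the hypothesis.** A reader might infer that biopsy does change who conceives, and that the per-pregnancy results will therefore mislead. The documents do not support that. The Discussion calls the therapeutic effect uncertain, and the sample size section speaks of growing uncertainty. If biopsy does not change who conceives, this bias does not arise.
- **The size rests on assumed loss rates.** The PIP-UE section applies one 19% shortfall to both arms, and at that value the ratio is 1.00. This stands: the range is an illustration, not a forecast.
- **The per-woman version has its own limit.** At equal loss the per-woman miscarriage ratio is about 2.8 with no pregnancy harmed, simply because more women are pregnant. That is further from 1 than any per-pregnancy ratio in the table. This stands too, and is the reason to keep the per-pregnancy rates as context and not delete them.

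The valid per-woman comparisons are already planned. But the article does not say which version governs if the two disagree, and at q = 5% they point in opposite directions (0.53 and 1.47).

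**Conclusion.** The concern holds in conditional form. Applied as written, the plan attaches risk ratios and p values to three secondary outcomes in a subset defined after randomisation. If biopsy changes who conceives, as the trials hypothesise, and the added pregnancies carry a different risk, these comparisons are biased. In the PIP-UE illustration selection alone moves the miscarriage ratio to between about 0.5 and 1.7 for an assumed 5% to 40% loss in the added pregnancies. Both conditions are needed; if either fails there is no distortion of this kind.

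It would be too strong to say that the safety analysis as a whole is invalid, or that a false signal of harm is to be expected. The primary outcome is per woman randomised, the per-woman versions of all three outcomes are specified, and the direction of any bias is unknown. This is a matter of labelling and inference for secondary outcomes, worth correcting because it is cheap.

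**What to change.** - In Outcomes and in Statistical analysis, state that per-clinical-pregnancy results for multiple pregnancy, ectopic pregnancy and miscarriage are descriptive by arm, conditional on pregnancy and not randomised comparisons, and are given without p values.
- Base between-arm inference for these outcomes on women randomised. Report it beside clinical pregnancy and live birth, and note that miscarriage per woman rises whenever more women conceive.

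The cost is about one sentence in each section. No new data and no change of sample size are needed. The downside is that there would be no formal test of risk per pregnancy, so readers who want that figure would have only the descriptive rates.

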### Eligibility criteria

#### Inclusion criteria

Women who meet the following inclusion criteria are eligible to take part in the PIP studies:

##### PIP-IVF

Planning to undergo autologous embryo transfer

Fertility clinics that routinely perform single embryo transfers are eligible to recruit for the PIP-IVF study. As per the pragmatic nature of the PIP studies, a number of women undergoing double embryo transfers will be recruited. The proportion of women in PIP-IVF who are undergoing double embryo transfers should not exceed the normal proportion of women who undergo double embryo transfers at the participating clinics (no more than 20 % [3]).

##### PIP-UE

In a relationship where the couple is having regular, unprotected sexual intercourse and pregnancy is desired42 years of age or younger at the time of randomisationDiagnosed with unexplained infertility, must meet all of:Unsuccessfully trying to conceive for at least 12 months,Normal ovulation (21–42 day menstrual cycles with variation <8 days),Male partner has had a normal semen analysis in the last five years according to WHO criteria [36] (volume ≥1.5 ml, progressive motility ≥32 %, concentration ≥15 million/ml) or total motile count >10 millionHave either:Two ovaries and two probably patent fallopian tubes (normally confirmed by laparoscopy or hysterosalpingography (HSG))A previous intrauterine pregnancy, and no subsequent surgery, infection or ectopic pregnancy that may reduce tubal patencyBody mass index (BMI) ≤ 35 kg/m^2^Willing and able to have regular sexual intercourse in the cycle in which the procedure is performed, and for two cycles following the procedure.

